### Sample size calculation

Linear mixed effect modeling with two conditions and three repeated measures will be conducted to analyze the effects on mentalizing abilities and stress regulation. The sample size is estimated based on previous studies measuring the mentalizing ability of perspective-taking using the Perspective Taking (PT) subscale of the Interpersonal Reactivity Index (IRI) and stress regulation using the Lifestress Inventory (LI) among people with intellectual disabilities. With the means used from both measures (for means, see [37, 38]), a desired power of 0.90, and α = 0.05, it is estimated that around 144 participants are needed, as calculated in GLIMMPSE [39]. Because there are three assessments, dropout of 20% will be taken into account. Thus, 172 participants will be recruited and randomized into two groups of approximately 86 participants in each group.

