### Study procedure and randomization

Individuals who sign up for the research both via the care organization as well as via the Internet or any other route and who meet the inclusion criteria will receive an information brochure. Persons who want to participate in the study are asked to sign the consent form and return it to the researcher. In case of legal incapacitation, the legal representative of the participant is asked to sign and return a consent form on behalf of the participant.

Data collection for each participant takes 12–14 weeks. Participants will be assessed at baseline (T0), post intervention (T1, 5 weeks after baseline), and follow up (T2, 6–8 weeks after T1). During all three assessments, participants fill out a set of digital questionnaires (for all measurements, see Measures). A software program (e.g. Qualtrics or Survalyzer) will be used to gather data through the digital questionnaires. Completing the questionnaires will take up to 90 min per assessment. During all assessments, an independent researcher is present to assist the participants with completing the questionnaire at home or in their care home. The researchers will follow a standard protocol on how to assist the participants.

After informed consent and baseline assessment, blind for intervention, participants will be individually randomized into two groups using stratified randomization in combination with block randomization with varying block sizes of 4 and 6. To balance contextual factors, randomization will be stratified with regard to care organization. An independent researcher will produce the allocation schedule using a computerized random number generator and afterward conceal the schedule for the researchers. Blinding is only possible for the baseline assessment and, after that, both participants and the researchers will know to which group participants have been assigned.

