## Data analysis

All statistical analysis will be conducted using SPSS version 24.0. Descriptive statistics will give insight into the characteristics of the participants. Before analyzing, outliers will be checked and, if necessary, winsorized and partial intention-to-treat analysis will be performed. Demographic variables are used to test for differences in baseline characteristics between the experimental and control groups, and are added as covariates if differences are found. For social validity, average item scores are reported.

Primary and secondary outcome measures of the study (i.e. mentalizing abilities and stress regulation) will be assessed using linear mixed-effects modeling. With Subject at the highest level and Group, Time, and the Group × Time interaction entered as fixed effects, a mixed model fits into SPSS. Furthermore, compliance will be controlled for through anonymous digital game statistics (how often the computer game is completed) and care organization will be the stratifying variable.

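### The mixed model leaves the group means at T0 free although T0 precedes randomization, so the treatment effect is a valid but less precise change-score contrast.

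*Protocol article*

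**What the plan says.** The Sample size calculation section announces that "Linear mixed effect modeling with two conditions and three repeated measures will be conducted". The Measures section collects every primary and secondary outcome at T0, T1 and T2, so T0 is one of the modelled responses. The Data analysis section then gives the fixed effects: "With Subject at the highest level and Group, Time, and the Group × Time interaction entered as fixed effects".

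The order of events is in Study procedure and randomization: "After informed consent and baseline assessment, blind for intervention, participants will be individually randomized into two groups".

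Two other statements in Data analysis bear on the point. The covariate rule reads "Demographic variables are used to test for differences in baseline characteristics between the experimental and control groups, and are added as covariates if differences are", its last clause making inclusion depend on an observed difference; the outcome's own T0 score is not named. The section also says that compliance, taken from game statistics, will be controlled for. It does not say which term of the model is the treatment effect, but with these fixed effects only Group × Time can carry it.

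**The concern.** In a randomized trial with a pre-randomization baseline, the two groups have the same expected T0 score by design. A Group main effect next to a full Group × Time interaction ignores this and estimates a separate T0 mean for each group. The interaction at T1 is then the between-group difference in change from T0. That contrast subtracts the whole observed T0 difference, which is chance alone, instead of only the part that predicts T1.

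At stake is precision on every primary and secondary measure. The T0 scores are collected anyway, so the gain needs no further participants or visits. The covariate rule does not recover the loss, because it concerns demographic variables only.

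**Working it through.** **The plan's own figure.** The article states "a desired power of 0.90, and α = 0.05, it is estimated that around 144 participants are needed, as calculated in GLIMMPSE". This cannot be reproduced: no means, SDs, correlation or tested contrast are given, only a pointer to cited sources. The figures below therefore compare two analyses of the same data and do not test 144.

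**Inputs.** From the article: two equal groups, three assessments, power 0.90, alpha 0.05 and 144 participants before dropout (72 per group). Assumed: two-sided alpha, SD 1, and compound symmetry with correlation rho, varied because no value is given.

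**Variance of the T1 effect, n = 72 per group, complete data.**
- Planned model (free T0 means): 2(1−rho) × 2/n.
- Common T0 mean: (1−rho²) × 2/n.
- Ratio, common to planned: (1−rho²) / [2(1−rho)] = (1+rho)/2, below 1 for every rho below 1.

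At rho 0.5 the planned variance is 2 × 0.5 × 2/72 = 0.0278 and the common-mean variance is 0.75 × 2/72 = 0.0208, a ratio of 0.75.

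**Power.** If the planned contrast has 0.90 power, its noncentrality is 1.960 + 1.282 = 3.2415. With a common T0 mean, power is Φ(3.2415/√[(1+rho)/2] − 1.960), and the number needed for 0.90 power is 144 × (1+rho)/2, rounded up.

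| rho (assumed) | variance ratio | power | N for 0.90 power |
|---|---|---|---|
| 0.3 | 0.65 | 0.98 | 94 |
| 0.5 | 0.75 | 0.96 | 108 |
| 0.7 | 0.85 | 0.94 | 123 |
| 0.9 | 0.95 | 0.91 | 137 |

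**Check by fitting.** In one simulated complete data set (72 per group, rho 0.6), the random-intercept Group × Time estimate at T1 equalled the difference in mean change exactly (0.0929 both ways). The common-mean fit had 0.77 times its variance; theory gives 0.80.

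**With dropout.** With 86 per group and an assumed 10% lost by T1 and 20% by T2, the T1 ratio is 0.77 at rho 0.5 and 0.86 at rho 0.7. The T2 ratio is 0.79 and 0.87.

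**Does deleting Group suffice?** No. With Time as a factor, Group + Time + Group × Time and Time + Group × Time span the same six-dimensional space, one mean per group and time. The fit is identical. The common-mean model has five: three time means plus a group difference at T1 and one at T2.

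**The compliance covariate.** Suppose compliance enters as one value per person, zero for waitlist controls, with an assumed mean of 6 and SD of 2 levels in the game group. It then largely stands in for Group and reopens the T0 difference. The variance ratio rises to about 0.95 at rho 0.5 (instead of 0.75) and about 0.97 at rho 0.7 (instead of 0.85). The planned model's Group × Time variance is unchanged by this covariate.

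**The case against.** The strongest reply is that nothing in the plan is invalid: Group, Time and Group × Time is a common longitudinal model. That stands, and the point is about efficiency only. A reader might infer that free T0 means bias the result. The documents do not support that. Given an observed T0 imbalance d, the change contrast shifts by (1−rho)d; for a one-standard-error imbalance at rho 0.5, that is 0.5 × √(2/72) = 0.08 SD. The shift averages to zero over randomizations.

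A reader might also infer that the change would make good a shortfall in sample size. No shortfall follows from this point. GLIMMPSE may have been run on this same interaction, in which case the planned power already belongs to the stated model. How 144 was raised to 172 is a separate question.

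The size of the gain is unknown. At rho 0.9 power moves only from 0.90 to 0.91; at rho 0.3 it moves to 0.98. This stands, and is why a range is given.

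It can also be said that an article leaves baseline handling to a fuller document. Here, however, the fixed effects are stated, so the choice can be reviewed. The objection that compliance adjustment would undo the gain is correct and is dealt with in the fix.

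**Conclusion.** The point holds as a loss of precision in a valid analysis. The stated model gives a change-score contrast (exactly so with complete data), and the article names no use of the T0 outcome as a covariate. A common T0 mean would cut the T1 variance by a share (1−rho)/2: 35% at rho 0.3, 25% at 0.5, 15% at 0.7 and 5% at 0.9. These figures rest on compound symmetry and an assumed rho; the power figures also assume that the planned contrast has exactly 0.90 power with 144 participants at two-sided 0.05. The gain appears only if the compliance variable is absent from the primary model. The change is worth making before the data are analysed, but the trial's validity does not depend on it.

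**What to change.** State the primary model in one of two forms:
1. T0, T1 and T2 as outcomes, with Time and two explicit indicators, Group×T1 and Group×T2, and no group term at T0. The indicators have to be built by hand in SPSS, since removing Group from the factorial specification leaves the fit as it was.
2. T1 and T2 as outcomes, with Group, Time, Group × Time, and the T0 score by Time as covariate.

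The two are close but need not agree exactly in every data set, so one should be named in advance. Report the between-group differences at T1 and T2 as the treatment effects. Keep care organization in the model as the stratification factor.

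Move compliance to a secondary analysis. It is measured after randomization; in form 1 it removes most of the gain, and in form 2 it competes directly with Group for the treatment effect.

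The cost is two derived variables and a few lines of syntax and plan wording, plus the decision on compliance. No new data, visits or participants are needed.

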## Hypotheses

The serious game ‘You & I’ is hypothesized to have a positive effect on mentalizing abilities, including the regulation of stress, in adults with MBID. The primary hypothesis is that being randomly assigned to the experimental group that plays the serious game will be associated with an improvement of the mentalizing abilities in adults with MBID as compared to being assigned to a waitlist control group. The secondary hypothesis is that being randomly assigned to the experimental group playing the serious game will be associated with an improvement of stress regulation in adults with MBID.

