After randomization, participants within the experimental group will be offered the serious game ‘You & I’, while participants within the control group will be placed on a waitlist. Participants from the experimental group will be asked to play the serious game on their own computer device at home or on a computer device of their care home. They have to complete eight gaming levels within 4 weeks, playing the game twice a week. To remind the participants to play the game, they will receive an impersonal email or text message on their phone twice a week asking them whether they have already played the game. Anonymous digital game statistics will measure the compliance of the participants (how often the computer game has been completed). After 4 weeks, the post-intervention assessment is administered, and 6–8 weeks later the participants complete the follow-up assessment. Participants from the control group can play the serious game after they have completed the follow-up assessment.

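### Adjusting the primary and secondary models for game completions, a consequence of allocation, can distort or remove the effect of assignment, depending on a coding the protocol leaves open

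*Protocol article*

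**What the plan says.** All places are in the protocol article.

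- **Data analysis**, on the model for both outcomes: "With Subject at the highest level and Group, Time, and the Group × Time interaction entered as fixed effects, a mixed model fits into SPSS". The next sentence adds that "compliance will be controlled for through anonymous digital game statistics (how often the computer game is completed", and names care organization as stratifying variable in the same breath. Nothing confines the compliance term to a per-protocol, sensitivity or dose-response analysis, and its form (main effect, interaction with Time, or time-varying) is not given.
- **Study procedure and randomization**, on when play occurs: "After randomization, participants within the experimental group will be offered the serious game", with the dose described as "They have to complete eight gaming levels within 4 weeks, playing the game twice a week". For the other arm: "Participants from the control group can play the serious game after they have completed the follow-up assessment".
- **Study procedure and randomization**, on how play is recorded: "Anonymous digital game statistics will measure the compliance of the participants".
- **Hypotheses**, on what the trial sets out to show first: "being randomly assigned to the experimental group that plays the serious game will be associated with an improvement of the mentalizing abilities". The comparison is with assignment to the waitlist.
- **Data analysis**, on the analysis set: "if necessary, winsorized and partial intention-to-treat analysis will be performed". What makes it partial is not explained.

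**The concern.** The hypothesis asks what assignment to the game does. Playing is the route by which assignment can work, and only one arm can play during the trial. Controls do not vary in completions, so the coefficient for completions is learned entirely from differences among experimental participants who chose to play more or less. Holding completions fixed therefore conditions on the pathway, and it replaces a randomized comparison with one that depends on who chooses to play. The adjusted contrast is neither the effect of assignment nor a valid effect of playing.

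At stake is the main inference for both outcomes. Because the coding is open, the answer could also depend on a choice made after the data are seen.

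**Working it through.** **Plan's own figures.** The plan states no figure for this adjustment. Its sample size of 144 before dropout cannot be reproduced, because the article gives no effect size, SD or correlation. Everything below is illustration under stated assumptions.

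**Inputs.** From the article: 144 participants, so 72 per arm; three visits; power 0.90; α = 0.05 (taken as two-sided); eight levels. Assumed: SD 1, within-subject correlation 0.5, and a standardized effect that gives about 90% power with 72 per arm, (1.96 + 1.2816) × √(2/72) = 0.54. Completions are binomial out of eight in the experimental arm, with completion probability 0.6, 0.8 or 0.9, and zero in controls. Generalized least squares, 1,500 replicates.

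**1. Benefit proportional to levels played.** Conditional on completions, Group × T1 is the effect at zero levels, which is zero by construction. Entries are the Group × T1 estimate (SE) and power.

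| Completions in the model | p = 0.6 | p = 0.8 | p = 0.9 |
|---|---|---|---|
| Not included | 0.536 (0.167), 0.89 | 0.538 (0.167), 0.90 | 0.540 (0.167), 0.91 |
| Time-constant main effect | 0.536 (0.167), 0.89 | 0.538 (0.167), 0.90 | 0.540 (0.167), 0.91 |
| Completions × Time | −0.018 (0.448), 0.06 | −0.010 (0.701), 0.05 | 0.026 (1.037), 0.05 |
| Time-varying | −0.016 (0.338), 0.06 | 0.001 (0.510), 0.05 | 0.007 (0.743), 0.05 |

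A second set of assumptions (correlation 0.6, effect 0.5 SD, six of eight levels on average, SD 2) agrees: 0.491 (0.149) unadjusted and with a main effect, −0.003 (0.354) with completions × Time, −0.014 (0.305) time-varying.

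**2. Benefit the same at any dose (p = 0.8).** The estimate survives: 0.513 with completions × Time and 0.521 time-varying. The SEs are 0.700 and 0.509, and power is 0.12 and 0.19.

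The loss of precision follows from collinearity. With mean m and variance s² of completions in the experimental arm, VIF = 1 + 0.25m²/(0.5s²).
- p = 0.6: m = 4.8, s² = 1.92, VIF = 1 + 5.76/0.96 = 7, SE × 2.65, so 0.167 × 2.65 = 0.44.
- p = 0.8: m = 6.4, s² = 1.28, VIF = 1 + 10.24/0.64 = 17, SE × 4.12, so 0.69.
- m = 6, s = 2: VIF = 1 + 9/2 = 5.5, SE × 2.345, power Φ(3.2415/2.345 − 1.96) = Φ(−0.58) = 0.28.

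The first two match the simulated completions × Time values of 0.448 and 0.701. The time-varying coding costs less, but still about doubles the SE at p = 0.6 (0.338/0.167 = 2.02).

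**3. Time-constant main effect.** Group × Time is a within-person contrast here, so a person-level constant leaves it alone. The covariate's slope averages the three visits' slopes, (0 + b + b)/3 = 2b/3. At mean completions this absorbs 2/3 × 0.54 = 0.36. The predicted baseline contrast is −0.36, and the adjusted T1 contrast is 0.54 − 0.36 = 0.18. Simulated across the three values of p: baseline −0.355 to −0.387; T1 contrast 0.188 to 0.154, with power 0.08 to 0.05. With about 20% dropout related to low completion (p = 0.8), Group × T1 is still 0.546 against 0.547 unadjusted, and the T1 contrast is 0.220.

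**4. Self-selected play.** The direction of bias is not predictable. With completion probability rising 0.1 per SD of baseline score (p = 0.8), Group × T1 is 1.371 (SE 0.593) with completions × Time and −0.005 (0.436) time-varying. Under the second set of assumptions, with levels correlated 0.4 with stable ability, it is about −0.01 with completions × Time, −0.39 time-varying and 0.49 with a main effect.

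**The case against.** The strongest reply is that the article lists only Group, Time and their interaction, and mentions no interaction of compliance with Time. One count per participant added as a plain covariate is at least as natural a reading, and then the Group × Time test keeps its estimate and power. This stands. A reader might infer that the adjustment necessarily removes the treatment effect, but the text does not support that without knowing the coding. What remains under the benign reading is the biased Group term and adjusted T1 contrast, with no gain for Group × Time.

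A reader might also infer that the game would be made to look harmful. In the three-visit model a clearly negative estimate appeared under only one coding and one pattern of self-selection (about −0.39), and another pattern pushed the estimate up. Harm is a possibility, not a prediction.

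The magnitudes are assumed. A zero estimate needs benefit strictly proportional to levels. The fall to 12–28% power needs a dose-independent benefit together with a term acting on change. It is also not clear that the plan's completion count means levels out of eight. All of this stands, but the direction follows from the structure of the model.

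Finally, a reader might infer from the word anonymous that play cannot be linked to outcomes. The Data management and monitoring section says each participant has a unique identification number and that data are processed under it, so the word may mean pseudonymized. The article does not say that the game logs carry the number, so this is a clarification and not a demonstrated impossibility.

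An unseen analysis plan does not answer the main point, because the article itself states the rule and places it with the main model.

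**Conclusion.** The point holds in conditional form. As written, the primary and secondary models adjust for a consequence of allocation that is zero by design for all controls until after T2, so they need not estimate the effect of assignment that the hypothesis names.

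- If the term acts on post-baseline outcomes, Group × Time can go from about 0.5 SD to about 0 under dose-proportional benefit. Under dose-independent benefit its SE is at least doubled.
- If it is a time-constant main effect, Group × Time is unchanged, but the adjusted T1 contrast loses about two-thirds of the effect and a false baseline difference appears.

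No coding improves the primary estimate. The sizes rest on the assumed effect (about 0.5 SD), correlation (0.5 to 0.6), completion rates (60–90%) and dose–benefit relation, none of which the article gives.

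**What to change.** 1. Delete compliance from the primary and secondary models. State that the primary estimate is Group × Time by allocation in all randomized participants, and define or drop the qualifier partial on intention-to-treat.
2. Use completion counts only in a labelled secondary analysis, for example a complier-average causal effect with assignment as the instrument, or a descriptive dose-response within the experimental arm. The choice between these can be left to the full analysis plan.
3. State that the game statistics are linked to participants through the study identification number, and replace the word anonymous if pseudonymized is meant.

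The cost is a sentence or two in the analysis section and, if the game logs do not already carry the identification number, arranging that they do. No further participants or assessments are needed.

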## Data management and monitoring

Data will be collected using online survey software. Computerized data will be stored on a secured server of Vrije Universiteit Amsterdam. The participant’s privacy is guaranteed by assigning a unique identification number to every participant. Data will be processed using these identification numbers. All researchers who will work with the research data will sign a nondisclosure agreement, stating that they will not share personal details of participants with a third party. The handling of the data will comply with the General Data Protection Regulation (GDPR). A data management plan was submitted and accepted by the funding organization of the study (ZonMw; project number 845004004). This study is also embedded in the Amsterdam Public Health (APH) Research Institute. The quality committee of APH offers a handbook to safeguard the quality of the research and performs random audits.

## Ethical considerations

Ethical approval was given by the Medical Ethics Committee of the University Medical Center Amsterdam location VUmc, the Netherlands (METc VUmc 2018.007, NL60353.029.17) and the Institutional Review Board of the Faculty of Behavioral and Movement Sciences of the Vrije Universiteit Amsterdam (VCWE-2017-171). Potential future changes to the study will be proposed to the Medical Ethics Committee as amendments, and will be described and discussed in publications of this study hereafter.

